## Abstract

**Background:**

Haemodialysis (HD) is one of the life-saving options for patients with end stage renal disease but demand for this treatment exceeds capacity in publicly funded hospitals. One novel approach to addressing this problem is through a shared-care model whereby government hospitals partner with qualified private HD service providers to increase the accessibility of HD for needy patients. The aim of this study is to evaluate and enhance the quality of care (QOC) provided in such a shared-care programme in Hong Kong, the Haemodialysis Public-Private Partnership Programme (HD-PPP).

**Methods/Design:**

This is a longitudinal study based on Action Learning and Audit Spiral methodologies to measure the achievement of pre-set target standards for the HD-PPP programme over three evaluation cycles. The QOC evaluation framework is comprised of structure, process and outcome criteria with target standards in each domain developed from review of the evidence and in close collaboration with the HD-PPP working group. During each evaluation cycle, coordinators of each study site complete a questionnaire to determine adherence with structural criteria of care. Process and clinical outcomes, such as adverse events and dialysis adequacy, are extracted from the patient records of consenting study participants while face-to-face interviews are conducted to ascertain patient-reported outcomes such as self-efficacy and health-related quality of life.

**Discussion:**

The study relies on the successful implementation of partnership-based action research to develop an evidence-based and pragmatic framework for evaluation of quality of care in an iterative fashion, and to use it to identify possible areas of quality enhancements in a shared-care programme for HD patients. The approach we take in this study emphasizes partnership and engagement with the clinical and administrative programme team, a robust but flexible evaluation framework, direct observation and the potential to realize positive change. The experience will be useful to inform the process of coordinating research studies involving multiple stakeholders and results will help to guide service planning and policy decision making.

**Trial registration:**

US Clinical Trial Registry NCT02307903

**Electronic supplementary material:**

The online version of this article (doi:10.1186/s12882-016-0284-9) contains supplementary material, which is available to authorized users.

## Background

End-stage renal disease (ESRD) is a state in which the kidneys do not function sufficiently to sustain life. Patients with ESRD require renal transplantation, haemodialysis or peritoneal dialysis as a form of renal replacement therapy (RRT) in order to survive [1]. Worldwide prevalence of ESRD is anticipated to rise in tandem with the increasing prevalence of diabetes mellitus and hypertension globally which will drive future demand for RRT [2] and underlines the necessity of developing approaches to meet this need [3]. Haemodialysis (HD) is generally the preferred mode of therapy when renal transplantation is not possible, but it is expensive and resource-intensive [4]. In Hong Kong the Hospital Authority (HA), which is the government body which oversees public hospitals, has thereby adopted a “peritoneal dialysis (PD) first” policy for ESRD patients eligible for RRT [5]. HD is currently reserved for ESRD patients who have failed or have contraindications for PD.

HD has traditionally been performed in hospital-based settings with increasing demand necessitating expansion to satellite clinics (either hospital-linked public clinics or privately funded independent clinics) or home-based HD. A review of satellite HD clinics in the United Kingdom found no significant differences in clinical processes of care or clinical outcomes compared with hospital clinics [6]. A further systematic review that found that both home and satellite unit HD were somewhat better that hospital HD in most measures of effectiveness including quality of life and survival [7]. This, coupled with better accessibility and higher patient acceptability, suggests that satellite community clinics have the potential to be effective alternatives to traditional in-hospital units for HD patients. On this background, a new service provision model was introduced in Hong Kong by the HA in 2010 to expand the capacity to accommodate patients with ESRD needing HD. The Haemodialysis Public-Private Partnership (HD-PPP) programme [8] involves the sharing of care of HD patients between public hospital-based renal units and qualified community-based HD clinics. This programme allows participants to receive HD treatment in the community, while continuing to receive usual follow up care at the partner public hospital.

The target population for the HD-PPP programme include existing HA patients who fulfill the designated clinical criteria and are currently receiving HD in HA hospitals, new ESRD patients with contraindications for PD or patients who are currently on PD but are at risk of treatment failure. Eligible patients who choose to enroll in the programme will receive HD treatment in their selected community HD centre run by a private or charitable organization, and will pay no additional fees. The frequency of dialysis and other medical decisions would be overseen by the HA nephrologist looking after that particular patient. HD-PPP participants are followed up regularly at the renal specialist outpatient clinic (SOPC) to monitor their HD adequacy, renal function and other relevant clinical parameters.

As part of the development of a new health care service programme, it is important to include an evaluation component, best undertaken by an independent third party working in close collaboration with the programme planners, providers and administrators, to examine whether the programme delivers the care that it is intended to deliver, to the desired standard. The effectiveness of the programme in benefitting the health of service recipients and the sustainability of the programme can also be determined over a longer period of time. Such findings will provide valuable evidence to help those providing front-line care as well as those developing and coordinating the programme to improve the quality of patient care, and to support the continued funding and expansion of the programme.

### Aim of study

The aim of this study is to evaluate the quality of care and effectiveness of the HD-PPP programme for HD patients under the shared care of publically-funded hospital renal units and affiliated community HD centres in Hong Kong. An evidence-based, structured and comprehensive evaluation framework will be developed and used to identify areas for quality enhancement.

The objectives of the study are to:Review and identify the structure, process and outcome indicators of QOC;Identify the criterion and set the target standard for each indicator;Compare the observed standards against the target standards;Identify any on-site problems related to implementation of the programmeProvide feedback on the QOC of the programme;Identify possible areas for improvement;Give recommendations for enhancement of service delivery.

### Hypotheses

The following hypotheses will be tested:The criteria on structure and process should be achieved by all participating HA renal units and community HD centres;The dialysis for patients should be adequately maintained (Kt/V ≥ 1.2 for patients receiving 3 HD sessions per week or ≥ 1.8 for those receiving 2 HD sessions per week) after 12, 24, 36 and 48 months in the programme;Patients in the programme should report no worse outcomes as patients managed by usual care in the HA (control);

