#### Evaluation on outcomes of care

Anonymized data on clinical parameters at baseline, 12, 24, 36, 48 and 60 months after enrollment will be retrieved from the CMS by the HA statistics team.

For patient-reported outcomes, HD-PPP subjects and non-HD-PPP subjects will be invited in person at the community centre/renal unit to complete a telephone/face-to-face survey on health-related quality of life at enrolment into the HD-PPP (or equivalent time for non-HD-PPP), and then again at 12, 24, 36, 48 and 60 months. The follow up surveys will also include questions assessing patient enablement and global rating of change in health condition. The trained research assistant administering the patient-reported outcomes questionnaire survey will also obtain written informed consent from each patient prior to commencing the survey.

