#### Secondary

Clinical outcomes include dialysis adequacy and blood haemoglobin.Patient reported outcomes (PRO) are measured by the change in Short Form-12 version 2 (SF-12v2) scores, the Patient Enablement Instrument (PEI) and Global Rating Scale (GRS) scores at baseline and after 12 months.

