### Data analysis

Descriptive statistics on standard of care will be calculated including the percentage of centres meeting each structure criterion, percentage of subjects enrolled, dropped out, receiving criterion process including HD, and percentage of subjects achieving each outcome criterion.The difference in clinical and PRO of patients who take part in the HD-PPP programme at baseline, 12, 24, 36 and 48 months will be compared by paired sample t-tests.Independent sample t-test or chi-square test as appropriate will be used to compare the clinical outcomes between HD-PPP participants and control patients.Independent sample t-test or chi square test as appropriate will be used to compare the clinical outcomes between results achieved in different evaluation cycles.

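### Hypothesis 3 claims outcomes no worse than usual care, but the listed analyses give no valid route to that conclusion and never compare patient-reported outcomes with control

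*Protocol article*

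**What the plan says.** The Hypotheses section opens with "The following hypotheses will be tested". The third hypothesis, the only one that refers to a control group, is: "Patients in the programme should report no worse outcomes as patients managed by usual care in the HA (control".

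Under Evaluation on outcomes of care, the survey covers both groups: "HD-PPP subjects and non-HD-PPP subjects will be invited in person at the community centre/renal unit", at enrolment and then yearly to 60 months. The secondary outcomes list clinical outcomes first and PROs separately: "Patient reported outcomes (PRO) are measured by the change in Short Form-12 version 2 (SF-12v2) scores", together with the Patient Enablement Instrument (PEI) and the Global Rating Scale (GRS).

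The Data analysis section lists four items:
- descriptive percentages;
- paired t-tests over time within the programme, covering "The difference in clinical and PRO of patients who take part in the HD-PPP programme at baseline, 12, 24, 36 and 48 months";
- the comparison with control: "Independent sample t-test or chi-square test as appropriate will be used to compare the clinical outcomes between HD-PPP participants and control patients";
- the same kinds of test between evaluation cycles.

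Only the third item sets HD-PPP against control.

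**The concern.** Two things do not fit together.

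**Type of test.** The hypothesis is directional: the programme is not worse than usual care. A t-test or chi-square test, as ordinarily applied, takes no difference as its null. Failing to reject that null is not evidence for it, and non-significance becomes more likely as the data become fewer or noisier. The listed test can support the hypothesis only if the programme comes out significantly better.

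**Coverage.** The hypothesis speaks of what patients report. The between-group item covers clinical outcomes only, while PROs appear by name only in the within-programme item. Change over time among participants says nothing about how they stand against usual care.

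At stake is whether the study can answer its one question about usual care. Followed as listed, it would collect PRO data from controls with no stated comparative use, and a null clinical comparison would leave hypothesis 3 unresolved.

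**Working it through.** **Step 1. Hypothesis against analyses.** The article states no sample size, power, significance level or margin, so there is no figure to reproduce. The finding comes from the text.

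| Question | Protocol article |
|---|---|
| Is hypothesis 3 to be tested? | Yes (Hypotheses) |
| Are PROs collected in controls? | Yes (Evaluation on outcomes of care) |
| Are PROs compared between groups? | Not listed; the item is limited to clinical outcomes (Data analysis) |
| Does the term clinical outcomes include PROs? | Not in this article: Secondary outcomes lists them apart, and Data analysis names both in the paired item |
| What kind of between-group test? | A test of difference |

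If hypothesis 3 is read narrowly, as a PRO hypothesis, no listed analysis tests it. If it is read broadly, as all outcomes, it is tested for clinical outcomes only, by a test whose null result cannot confirm it.

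**Step 2. How uninformative a null result can be (illustration).**

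Inputs:
- Group size: 120 is the cumulative enrolment at 31 March 2012 (Discussion). It is not a planned sample size, and inclusion runs to 30 June 2014 (Subjects). The range 60 to 250 is assumed; final enrolment may be higher, and survey consent may lower the number with PROs.
- Assumed: two-sided 5% level; Kt/V adequacy of 85% in control and 75% in the programme; a PRO deficit of 0.3 SD. The PRO column shows what a test of difference would do if it were extended to PROs.

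Proportions: power = Φ{[|p1 − p2| − 1.96·√(2·p̄(1 − p̄)/n)] / √([p1(1 − p1) + p2(1 − p2)]/n)}, with p̄ = 0.80.

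At n = 120: √(2 × 0.80 × 0.20/120) = 0.0516 and √((0.1275 + 0.1875)/120) = 0.0512. Then (0.10 − 1.96 × 0.0516)/0.0512 = −0.02, so power is 0.49 and the test is non-significant 51% of the time.

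Means: two-sample t-test with noncentrality 0.3·√(n/2). At n = 120 this is 0.3 × 7.746 = 2.32, so power is 0.64 and the test is non-significant 36% of the time.

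| Per group | Non-significant, 85% vs 75% | Non-significant, 0.3 SD deficit |
|---|---|---|
| 60 | 72% | 63% |
| 120 | 51% | 36% |
| 200 | 29% | 15% |
| 250 | 20% | 8% |

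**Step 3. What a confidence interval could exclude at 120 per group.** For a mean in SD units, the 95% half-width is 1.96 × √(2/120) = 0.25 SD. For a proportion near 85%, it is 1.96 × √(2 × 0.85 × 0.15/120) = 0.09, or 9 percentage points. With an observed difference of zero, deficits up to about that size would remain compatible with the data.

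**The case against.** The strongest reply is that Data analysis never says how hypothesis 3 will be judged. It says only that tests "will be used to compare the clinical outcomes between HD-PPP participants and control patients". A reader might infer that the authors will declare the programme no worse after any non-significant test. The article does not say so, and that inference should not be charged to it. What remains is that the listed tests offer no valid route to the conclusion short of a significant advantage.

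A margin could also stand in a full protocol, an analysis plan or the evaluation framework in Additional file 1, none of which is shown. That is fair, and the absence of a margin is not the finding. The finding is that the tests and outcomes the article does name do not match the hypothesis it says will be tested.

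A third reply is that this is mainly an audit. The objectives compare observed with target standards, the three primary outcomes are proportions not defined as contrasts with control, and PROs are secondary. This stands and limits the severity. A reader might also infer that hypothesis 3 itself decides continuation and expansion of the programme; the Background and Discussion give that role to the evaluation as a whole.

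Finally, the illustrative rates rest on assumed effects and on an interim enrolment count. They fall considerably with larger groups, which is why the table runs to 250. If hypothesis 3 concerns PROs alone, the adequacy column is beside the point, and the missing PRO comparison is the main defect.

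**Conclusion.** The point holds. Hypothesis 3 is a no-worse claim presented for testing, but the only HD-PPP versus control analysis is a test of difference on clinical outcomes. PROs, though collected in both groups, have no listed comparison with control. Nothing else in the article repairs this.

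The size is illustrative. Under the assumptions in the working, a real deficit would give a non-significant result 20% to 72% of the time for adequacy (75% against 85%) and 8% to 63% of the time for a 0.3 SD PRO deficit, over 250 down to 60 per group. These are not the study's operating characteristics, since no planned number, effect or significance level is stated. The logical gap does not depend on them.

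It should be fixed. It affects the comparative part of the evaluation and leaves the three primary proportions untouched.

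**What to change.** Extend the third item of Data analysis to clinical outcomes and PROs (SF-12v2 physical and mental component summaries, PEI, GRS). Report each HD-PPP minus control difference with a two-sided 95% confidence interval. Then do one of the following:
- **Keep the claim.** Conclude no worse for an outcome only if its interval excludes a margin agreed with the programme working group before the control data are compared.
- **Drop the claim.** Reword hypothesis 3 as descriptive and report estimates and intervals without a no-worse conclusion.

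In either case, state that a non-significant difference will not be read as no worse.

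The cost is analysis wording and, under the first option, agreement on margins; no new data are needed. The real downside is that no worse becomes harder to conclude. At 120 per group with no true difference, power to exclude a margin of m SD is Φ(m·√60 − 1.96): 34% for 0.2 SD and 64% for 0.3 SD. For 80% power those margins need about 393 and 175 per group (2 × (1.96 + 0.84)²/m²). If numbers stay near 120, narrow margins are unlikely to be met and the descriptive option may be the more honest choice.

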## Methods/Design

The Action Learning [9] and Audit Spiral methodologies [10] will be used to carry out a systematic analysis of the QOC and to identify areas for enhancement in the HD-PPP programme. Donabedian’s taxonomy of QOC on structure, process and outcomes will be used as the template for the evaluation framework [11]. Three audit-spiral evaluation cycles will be carried out with feedback of results and a quality enhancement action plan to be implemented which aims at a higher level of QOC for each subsequent evaluation cycle.

Investigators will work together with the HD-PPP programme team to:Review and identify the structure, process and outcome indicators;Define the criterion and set the target standard for each indicator;Identify any on-site problems of implementation of the programme;Provide interim feedback on QOC of the programme;Identify possible actions for improvements;Compare the observed standards against the pre-set target standards;Make recommendations about the programme.

A QOC evaluation framework will be developed using an iterative approach, relying on reconciliation between the investigators and the programme providers to come to a consensus balancing evidence with practical considerations (Fig. 1). This framework lists the indicators of the structure (staff, facilities, organization, and management), process (what, when and how care is delivered), and outcomes (clinical and patient reported outcomes) with the required criteria and standard of care to be achieved (Additional file 1 – evaluation framework).

**Fig. 1 Fig1:**
[figure not shown]
Development of the evaluation framework: an iterative and collaborative process

### Subjects

All patients participating in the HD-PPP programme between 1 March 2010 and 30 June 2014 will be included in the evaluation on process of care. All HD-PPP participants and an equal number of non-HD-PPP participants (eligible for HD-PPP but not participating) matched by age and gender will be included in the evaluation on the outcomes of care. The non-HD-PPP subjects will be selected from the HA patient database by the HA Statistics and Workforce Planning Department. Subjects will be recruited via a letter from the HA or on-site by HKU research assistants upon enrolment in the HD-PPP programme.

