### Data collection

#### Evaluation on structure and process

The programme coordinator of each participating HA renal unit and community HD service provider will be asked to complete a written structure of care questionnaire. For some questions respondents are also requested to submit evidence to support their response. Incomplete or equivocal responses are clarified by telephone and further confirmation and cross-validation is made during scheduled site-visits. Anonymized data will be retrieved from the computerized medical record system (CMS) by the HA statistics team to determine the process of care indicators including dropout rate, attendance at hospitals or community HD centres, compliance with follow up monitoring as per protocol etc.

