### Potential to realize change

Even before results are compiled, the process of evaluation is a valuable exercise. It draws attention to practices that are taken for granted and motivates change. For example, Kt/V is widely recognized as a good indicator of dialysis adequacy and is used in clinical practice for patient management. It is also the primary clinical outcome indicator for this evaluation study. In the process of collecting data, we noted that it was not easy to collect Kt/V data because it is recorded in the open-text clinical consultation notes section of the electronic patient record or manually in paper record summaries, which cannot be extracted automatically. For patients in the HD-PPP a separate module of the electronic patient record has a designated Kt/V field but completing it is optional. To optimize the usefulness of Kt/V data, these need to be recorded in such a way that is systematic and easily retrievable by those involved in the patient’s care. This was discussed during a feedback meeting with the HD-PPP workgroup, leading to a pragmatic solution ensuring that Kt/V of every dialysis patient would be recorded annually in the electronic renal patient registry.

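### Dropout is reported as a crude percentage over staggered entry with no time horizon, so the figure depends on when patients enrolled as well as on retention

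*Protocol article*

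**What the plan says.** - **Population for the process evaluation (Subjects):** "All patients participating in the HD-PPP programme between 1 March 2010 and 30 June 2014 will be included". No minimum time in the programme is stated. One recruitment route is "on-site by HKU research assistants upon enrolment in the HD-PPP programme", so entry is spread over time.
- **Indicators (Evaluation on structure and process):** the hospital statistics team retrieves "process of care indicators including dropout rate, attendance at hospitals or community HD centres, compliance with follow up monitoring as per protocol". Dropout is called a rate, but no time base is given.
- **Statistic (Data analysis):** the descriptive summaries include the "percentage of subjects enrolled, dropped out, receiving criterion process including HD".
- **Contrast (Evaluation on outcomes of care):** the outcome data are anchored to each patient's own start: "Anonymized data on clinical parameters at baseline, 12, 24, 36, 48 and 60 months after enrollment". The process data have no such anchor.
- **Criteria (Methods/Design):** the framework lists the structure, process and outcome indicators "with the required criteria and standard of care to be achieved (Additional file 1 – evaluation framework". That file is not shown here.

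**The concern.** A percentage dropped out can be read only when it is known how long the patients were observed. Here possible time in the programme differs widely between patients, and the stated statistic ignores it. Two programmes with the same retention would report different dropout percentages if one recruited early and the other late. A single programme with stable retention would show a rising percentage if dropouts are accumulated since launch.

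This matters although the figure is descriptive. The study compares observed standards with pre-set targets, its third cycle is meant to assess whether standards of care are sustained, and the Discussion says the results should inform continuation and expansion of the programme. A rise in dropout that only reflects a longer period of observation could be taken for deterioration. A period with many recent joiners could look better than it is.

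**Working it through.** The article states no dropout figure, so there is none to reproduce. The check asks how far enrolment timing alone can move the stated statistic.

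**Inputs from the article.** The window from 1 March 2010 to 30 June 2014 is 1,583 days, which is 1,583/365.25 = 4.334 years or 52.0 months.

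**Assumptions, not in the article.** The dropout hazard *h* is constant and the same for all patients, the enrolment pattern is as stated below, dropout is the only way of leaving, and follow-up closes at the end of the period considered.

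**1. Growth with programme age.** With uniform entry over *T* years, the expected crude percentage is 1 − (1 − e^(−hT))/(hT). A 10% yearly risk gives h = −ln(0.9) = 0.1054.

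- T = 1: 1 − 0.1000/0.1054 = 5.1%.
- T = 52/12 = 4.333: hT = 0.4566 and e^(−0.4566) = 0.6335, so 1 − 0.3665/0.4566 = 19.7%.
- The 12-month risk is 10% at both times. The risk for a patient followed for the full 52 months is 1 − 0.9^4.333 = 36.7%. The crude percentage estimates neither.

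**2. Dependence on enrolment pattern.** For entry spread evenly from time *a* to *b*, the expected crude percentage at T = 4.334 is 1 − [e^(−h(T−b)) − e^(−h(T−a))]/[h(b−a)]. Example for h = 0.10 and entry in the first half (b = 2.167): 1 − (0.8052 − 0.6483)/0.2167 = 27.6%. In this table *h* is the hazard itself, so the 12-month risk is 1 − e^(−h).

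| Hazard per year | Entry in first half | Uniform entry | Entry in second half | First/second half | 12-month risk |
|---|---|---|---|---|---|
| 0.05 | 15.0% | 10.1% | 5.2% | 2.9 | 4.9% |
| 0.10 | 27.6% | 18.9% | 10.1% | 2.7 | 9.5% |
| 0.20 | 47.4% | 33.1% | 18.9% | 2.5 | 18.1% |

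Within a row retention is identical. Only the enrolment dates differ, and the crude percentage changes about 2.5- to 2.9-fold. The 12-month risk does not change with enrolment pattern, and neither does the rate per patient-year.

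**The case against.** **The figure is descriptive, and the article elsewhere says rate.** Both are true. The between-cycle tests in Data analysis cover clinical outcomes only, no dropout target is shown, and nothing says that each cycle is judged on a percentage accumulated since launch. The word rate leaves a time-based measure possible, but the analysis section names a percentage of subjects and gives no horizon. The ambiguity is therefore real, and its effect is on interpretation, not on a test.

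**30 June 2014 is not shown to be a data cutoff.** This also stands. The date bounds participation, no closing date is given for process data, and outcome data run to 60 months after enrolment. If dropout were followed well beyond June 2014, the figures above would change. Time at risk would still be unequal, because entry is staggered and no common horizon is set.

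**A stronger reading that a reader might infer** is that the primary proportion complying with the process of care is distorted in the same way, with recent joiners counted as failures for care not yet due. The article does not support this. The Subjects section says who enters the process evaluation, not who is in the denominator of each indicator. Compliance is with monitoring as per protocol, and a patient with nothing yet due has not breached a protocol. The one annual item mentioned, that "Kt/V of every dialysis patient would be recorded annually in the electronic renal patient registry", concerns a measure which the article lists apart from process compliance and calls its primary clinical outcome indicator.

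Even the direction is open. Suppose a once-a-year criterion with true compliance of 90% and uniform entry, so that 1/4.334 = 23% of patients have under 12 months. Scoring those patients as failures gives 0.90 × (1 − 0.231) = 69%, and leaving them out as not yet due gives 90%. An assumed criterion that every quarterly visit be met, at 98% per visit, gives 78% with first-half entry and 93% with second-half entry, so late joiners raise it. The definitions belong to Additional file 1, and their absence from a journal article is no error.

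**Conclusion.** The point holds for dropout. A crude percentage of subjects over a 52-month window with staggered entry and no horizon depends on enrolment timing as well as on retention, and would tend to rise with programme age if accumulated since launch. For illustration, it goes from about 5% at one year to about 20% at 52 months at a constant 10% yearly risk. That size rests on uniform entry, a constant risk and closure at the end of the window, none of which the article states. The dependence on timing does not rest on those particular values.

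For the primary compliance proportion, neither a bias nor its direction is established. All that is warranted there is a check against Additional file 1.

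**What to change.** 1. **Data analysis section:** replace the percentage dropped out by the cumulative incidence of dropout from each patient's enrolment date, at 12 months and later horizons. Censor patients still in the programme at a stated data cutoff, and treat death or transplant separately where these are not counted as dropout. A rate per patient-year is an acceptable alternative. Judge any dropout target on the chosen figure.
2. **Other process indicators:** confirm in Additional file 1 that each counts the patients for whom the care had fallen due, including those who later left. Do not limit the denominator to patients who stayed for the whole interval. That conditions on retention, drops early leavers whose compliance may have been poorest, and can inflate the proportion.

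**Cost:** a wording change and a little more analysis. The follow-up anchored at 12 months and later implies that enrolment dates are available, and a dropout indicator implies that exits are recorded, although the article does not say that exit dates are held. Estimates at later horizons will be less precise, because fewer patients are observed that long.
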